### Statistics

All collected data will be tabulated descriptively by study group and analyzed on an intention-to-treat basis. Comparisons between groups will be performed with the chi-squared test or the Fisher’s exact test, as appropriate. Ordinal qualitative variables or non-normal quantitative variables will be compared with the Wilcoxon sum of ranks test. Quantitative normal variables will be compared with the Student *t*-test. In particular, analysis of the primary efficacy criterion will be performed with Wilcoxon-Mann-Whitney sum of ranks test.

Consistently to other published studies [22], every participant in the treatment group will be compared with every participant in the control group and assigned a score resulting from each comparison.

Mortality takes precedence over VFD60, which takes precedence over IL6AUC. Two VFD60s will be considered different for the purpose of scoring only if their difference is larger than 5 days. Similarly, two IL6AUC’s measurements will be considered different only if their difference exceeds 10% of the smaller of the two.

These individual-comparison scores are added up to obtain the cumulative score primary endpoint for each participant. Scoring system for the primary endpoint is detailed in Additional file 4.

For the purpose of the study, mechanical ventilation will be defined as: invasive mechanical ventilation with endotracheal tube or tracheostomy and noninvasive positive pressure ventilation, including continuous positive airway pressure. High flow oxygen therapy through nasal cannula or tracheostomy will not be considered as mechanical ventilation.

The assumptions and methodology used for the determination of the sample size are detailed in Additional file 5 [35]. Given the results obtained, and adopting a conservative approach in order to compensate for the small residual random variation in the numerical assessment of the sample size, it appears that a sample size of 56 subjects per arm would be sufficient to obtain 80% power in detecting a difference in the composite endpoint, at a type 1 error level of 0.05, two-tail. With an attrition rate of 15%, a total of 132 patients in two equal groups of 66 patients each should be enrolled. This corresponds to a mean of 19 patients per center.

Primary and secondary endpoints will also be analyzed in subgroups, as defined below:

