∆EELV5-16/FRC ≥ 73% [18] during the PEEP trial∆EELV5-16/FRC < 73 %[23] during the PEEP trialRI ≥ 1 and < 1 across the range between the lowest and highest PEEP tested during the PEEP trialP/F ratio < 100 mmHg at study inclusionIL-6 > 400 pg/ml at study inclusion

All analyses will be performed at a 0.05 type I error level, two tail. All statistical analyses on secondary endpoints and on subgroups will be deemed to be exploratory in nature; for this reason, no correction of nominal significance levels for multiple inference will be applied.

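### As worded, the primary endpoint is scored only across arms and then given an ordinary rank-sum test, which does not hold the stated 5% error rate

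*Protocol article*

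**What the plan says.** All of this stands in the Statistics section of the protocol article.

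- **Scoring.** "every participant in the treatment group will be compared with every participant in the control group and assigned a score resulting from each comparison".
- **Endpoint per patient.** "These individual-comparison scores are added up to obtain the cumulative score primary endpoint for each participant".
- **Test.** "analysis of the primary efficacy criterion will be performed with Wilcoxon-Mann-Whitney sum of ranks test".
- **Hierarchy.** "Mortality takes precedence over VFD60, which takes precedence over IL6AUC". Two VFD60 values differ "only if their difference is larger than 5 days", and two IL-6 areas "only if their difference exceeds 10% of the smaller of the two".
- **Error rate.** "All analyses will be performed at a 0.05 type I error level, two tail".
- **Power.** "a sample size of 56 subjects per arm would be sufficient to obtain 80% power", raised to 66 per arm for 15% attrition.

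The section refers to Additional file 4 for the scoring system, to Additional file 5 for the sample-size method, and to a published trial as precedent. None of these is available here. The article mentions no comparison between patients of the same arm, and no permutation or U-statistic variance.

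**The concern.** A rank-sum test is valid when, under the null, each patient's score would be the same whichever arm the patient had been assigned to. Scores built only from opposite-arm comparisons fail this condition, because the allocation decides who each patient is compared with. A chance imbalance in outcomes moves all treated scores one way and all control scores the other, and the test reads the two shifts as separate evidence.

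This is the trial's only confirmatory test; the article calls its secondary and subgroup analyses exploratory. If the test were run as worded, a significant primary result could not be read at the 5% level.

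**Working it through.** **1. The plan's own figure.** 56 / (1 − 0.15) = 65.9, rounded up to 66 per arm and 132 in total. This reproduces. The 56 itself cannot be reproduced, because its assumptions are in Additional file 5.

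**2. Why the spread halves and the difference does not.** Let S(i,j) be +1, 0 or −1 for patient i against patient j, with S(j,i) = −S(i,j), and n patients per arm.

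- Within one arm the pairwise scores cancel, so they sum to zero. If W is the total of treated-versus-control scores, the mean treated score is W/n and the mean control score −W/n. This is so whether or not within-arm pairs are counted. The difference, 2W/n, is the same either way.
- For a continuous outcome without ties, a cross-arm score is roughly uniform on (−n, n), with SD n/√3. An all-patient score is roughly uniform on (−2n, 2n), with SD 2n/√3. At n = 56 these are 32.3 and 64.7.
- The same difference over half the spread doubles the test statistic. Nominal 5% then becomes 2 × [1 − Φ(1.96/2)] = 2 × [1 − Φ(0.98)] = 32.7%. This is a large-sample approximation; at 56 and 66 per arm the simulated rate for a continuous outcome is somewhat lower, 27.2% and 28.3%.

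**3. Simulation of the composite under no effect.** From the article: the hierarchy, both thresholds, 56 and 66 per arm, two-sided 0.05. Assumed: ICU mortality 25% or 40%; ventilation duration log-normal (median 14 days, log-SD 0.8); IL-6 area log-normal (log-SD 1.1); scores +1/0/−1; two ways of handling a pair of deaths. Each setting had 2,000 or 3,000 null trials.

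| Scoring | Two deaths separated by IL-6 | Two deaths tied |
|---|---|---|
| Opposite arm only, as worded | 27% to 31% | 37% to 69% |
| Each patient against all others | 4.4% to 5.7% | 4.4% to 5.7% |

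The last row gives one range over both ways of handling deaths.

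**4. Sensitivity.** With other assumed distributions for ventilator-free days and IL-6, and mortality from 10% to 70%, the rule as worded still rejected in 27% to 31% when IL-6 separated deaths. With deaths tied it rejected in 30% at 10% mortality and 85% to 89% at 50%. Graded scores of 3/2/1 for the three levels (an assumption) gave 34% to 62% for mortality of 10% to 50%. All-patient scoring stayed between 4.5% and 5.6% in these runs.

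**5. Why tied deaths make it worse.** Take 56 per arm with 22 treated and 23 control deaths, close to 40%. Each dead treated patient loses to the 56 − 23 = 33 surviving controls and scores −33. Each dead control loses to the 56 − 22 = 34 surviving treated patients and scores −34. A difference of one death thus ranks all 22 dead treated patients above all 23 dead controls. That turns 22 × 23 = 506 pairs from ties into wins and moves the rank-sum statistic by 506/2 = 253. Its null SD, ignoring the tie correction, is √(56 × 56 × 113/12) = 171.8, so the move is about 1.5 SD. With all-patient scoring the 45 deaths all score −(112 − 45) = −67 and stay tied.

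**The case against.** **The detailed rule is elsewhere.** The article's sentence may be a loose summary of a rule in Additional file 4 that compares every patient with all others, following the cited precedent. The error rate would then be about 5%. This stands as a limit on what can be claimed: a reader might infer that the trial's analysis will have a false-positive rate near 30%, and the documents do not establish that. It does not rescue the text, which states a specific rule and a specific test that do not fit together. The precedent cannot be checked here and would not make the stated combination valid.

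**A valid reading exists.** The Mann-Whitney statistic is itself a count over treated-versus-control pairs, so the authors may have meant one generalised U-test on wins and losses with its proper variance. That is possible. But the article builds a cumulative score for each participant and calls that the primary endpoint, which points to a rank-sum test on the sums.

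**The figures rest on assumptions.** Mortality, outcome distributions and the handling of two deaths are not given. The upper range (37% to 69%) needs two deaths to score as a tie, which the article does not say; its order of precedence, taken literally, would pass such a pair on to IL-6. The lower range does not depend much on the assumptions, since a plain continuous outcome gives nearly the same rate.

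**Power.** A reader might go on to infer that the trial's true power is far below 80%. If one picks an effect at which the rule as worded rejects about 80% of the time, the all-patient test has about 46% power, or 31% with deaths tied. These are hypothetical figures: they apply only if the sample-size simulation used the faulty rule, and nothing shown says that it did.

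**Conclusion.** The point holds for the procedure as the article words it. Opposite-arm scoring, summed per participant and followed by an ordinary Wilcoxon-Mann-Whitney test, does not control the two-sided 5% error rate. At the assumed ICU mortality of 25% to 40%, it rejects in about 27% to 31% of null trials if IL-6 separates two deaths and in about 37% to 69% if two deaths tie, against about 5% for all-patient scoring. The inflation appeared in every setting run; its exact size depends on assumed distributions and on scoring details that are not shown.

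Either way a correction is due. If Additional file 4 already uses all pairs, the article misstates the primary analysis. If it matches the article, the primary test is invalid. Whether the 80% power is affected, and by how much, cannot be determined from the documents.

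**What to change.** Replace the scoring sentence with one of the following.

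1. *Each participant is compared with every other participant in the trial, irrespective of arm; the scores are summed per participant and the sums are compared between arms with the Wilcoxon-Mann-Whitney (or Finkelstein-Schoenfeld) test.*
2. *Each treated participant is compared with each control; total wins minus losses is tested with a permutation or U-statistic variance.*

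Bring Additional file 4 into line, including how a pair of deaths is scored. Confirm that the simulation in Additional file 5 used the same valid procedure; if it did not, rerun it and restate the power, or the sample size needed for 80%.

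The cost is one sentence, a check of two files and possibly a rerun. No further data are needed for the analysis itself. The Trial status section says enrolment had not begun at submission. The price may be a less favourable power statement.

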### Safety/feasibility analysis, adverse events, and interruption of the trial

A Safety Monitoring Committee (SMC) will conduct an analysis to assess the safety and feasibility of the IPERPEEP protocol after 30 patients complete the study, and the study will be continued only if both safety and feasibility are established. In this assessment, no other data besides the criteria for safety and feasibility will be unblinded. The study will be considered feasible if at least 80% of the patients randomized to the intervention group will correctly undergo the allocated treatment according to the study protocol. The study will be considered safe if no serious adverse events related to treatment will be detected in the intervention group while the allocated treatment is ongoing.

Serious adverse events (SAE) will be defined as any event that is fatal or immediately life threatening, permanently disabling, severely incapacitating, or requires prolonged hospitalization or that may jeopardize the patient and requires medical or surgical intervention to prevent one of the outcomes listed above. SAE will be considered related to the treatment if the attending physician believes that they might be directly related to enrollment in the clinical trial. In particular, SAE’s will be considered to be study-related if the event follows a study procedure and could readily have been produced by the study procedure.

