## Background

Mechanical ventilation is the cornerstone treatment of the acute respiratory distress syndrome (ARDS). However, mechanical ventilation can itself initiate and worsen lung damage due to the so-called ventilator-induced lung injury (VILI), which is an inflammatory response that worsens lung function and contributes to the development of the organ dysfunction observed in ARDS patients [1]. Different strategies have been suggested to attenuate VILI: limiting tidal volume (*V*_T_); plateau and driving pressure mitigates lung injury and improves clinical outcome [2–6].

Low *V*_T_ may generate alveolar derecruitment and worsen oxygenation that can be reversed by the application of a positive end-expiratory pressure (PEEP) [7, 8]. It is widely accepted that PEEP setting should aim to a balance between alveolar recruitment (i.e., re-opening of collapsed alveolar units with increased lung volume available for tidal ventilation) and the damage unavoidably generated in the already open tissue. Hence, over the last decade, great effort has been made to identify the PEEP-setting strategy that balances the need for lung recruitment and PEEP-induced alveolar overdistension; PEEP titration methods based on respiratory system compliance [9–11], oxygenation, shunt value s[12, 13], and pressure-volume curve [14] have been proposed. Four different randomized studies comparing higher versus lower PEEP, with high PEEP set according to respiratory system mechanic s[10], oxygenation impairment [12, 13] or to maximize respiratory system complianc e[15], failed to detect a benefit. Higher PEEP however yielded a shorter time to successful weaning in the EXPRESS study, especially in most severe patients [10].

Despite a meta-analysis highlighted a survival benefit in more severe patients treated with higher PEE P[16], the most relevant drawback of such “universal” strategies is that lung recruitability has great inter-individual variability, with high PEEP enhancing lung injury in patients with low recruitability and low PEEP not fully exerting its beneficial effects in recruitable patients [14, 17–20]. Thus, a search for a tool to individualize PEEP on patient’s individual response appears warranted. In spite of encouraging results coming from a preliminary study [21], neither transpulmonary pressure-guided nor driving pressure-driven PEEP did provide benefits in larger trials [15, 22].

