### Data monitoring

Data monitoring will be performed for quality control purposes by an independent company not involved in the study (Clinical Trial Center, Rome, Italy). Amis of monitoring will be to evaluate the study progress and to verify the accuracy of data recording.

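### The stated safety criterion counts only physician-attributed SAEs in the intervention arm during treatment, so an excess of unattributed deaths or organ failure need not trigger it

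*Protocol article*

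**What the plan says.** The rule is in the Protocol article, section Safety/feasibility analysis, adverse events, and interruption of the trial.

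- **Timing.** A Safety Monitoring Committee "will conduct an analysis to assess the safety and feasibility of the IPERPEEP protocol after 30 patients complete the study". The trial continues only if both safety and feasibility are established.
- **Safety criterion.** Safety means that "no serious adverse events related to treatment will be detected in the intervention group while the allocated treatment is ongoing".
- **Relatedness.** "SAE will be considered related to the treatment if the attending physician believes that they might be directly related to enrollment in the clinical trial". A second wording counts an event as study-related "if the event follows a study procedure and could readily have been produced by the study procedure".
- **Data opened.** "In this assessment, no other data besides the criteria for safety and feasibility will be unblinded".

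Other parts of the article bear on this:

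- Study design states that the trial is open-label.
- PEEP setting protocols sets the assigned ventilation at a minimum of 72 hours, with use up to 14 days.
- Study endpoints lists ICU, hospital and 90-day mortality, SOFA and the number of failing organs. In-ICU mortality is part of the primary composite, and Statistics gives it precedence over the other components.
- Data monitoring is a separate activity: "Data monitoring will be performed for quality control purposes by an independent company not involved in the study".

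**The concern.** The Background describes ventilator-induced lung injury as a process "which is an inflammatory response that worsens lung function and contributes to the development of the organ dysfunction observed in ARDS patients". It also says that high PEEP can worsen injury in patients with low recruitability and that low PEEP can be insufficient in recruitable ones. Harm from a poorly matched PEEP would therefore resemble the disease under treatment. It would show as a difference in rates between arms, which a physician judging one patient cannot see.

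The stated criterion has no place for such a difference. It uses one arm, only attributed events, and only events during allocated treatment. An excess of deaths that nobody attributes, or that occur after allocated treatment ends, leaves the criterion satisfied. At stake is whether a rise in mortality under the experimental strategy would prompt any action before the final analysis.

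**Working it through.** **1. Share of patients beyond the described look.** The total is 132 (Statistics). It reproduces from 56 per arm and 15% attrition: 56/0.85 = 65.9, rounded up to 66, times 2 = 132. The look comes after 30 patients complete, so (132 − 30)/132 = 102/132 = 77% lie beyond it.

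**2. What the stated rule can register.** With 1:1 randomization, about 15 of the first 30 patients are in the intervention arm. Let p be the risk of death during allocated treatment and q the share of those deaths that the physician attributes to treatment. Considering deaths only, P(criterion met) = (1 − pq)^15. The article gives neither p nor q, so both are assumed.

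| p | q = 0 | q = 5% | q = 10% | q = 20% |
|---|---|---|---|---|
| 30% | 1.00 | 0.80 | 0.63 | 0.40 |
| 45% | 1.00 | 0.71 | 0.50 | 0.24 |
| 60% | 1.00 | 0.63 | 0.40 | 0.15 |

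The result is driven by q. If no death is attributed, the criterion is met at any mortality. If a fifth are attributed, it usually fails, and it does so even at 30% mortality, because it has no comparator. It responds to attribution habits as much as to harm.

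Zero attributed events in 15 patients is also weak reassurance: the one-sided 95% upper limit is 1 − 0.05^(1/15) = 18%.

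**3. What a by-arm review of deaths would add.** Assumptions: looks at 30, 66 and about 99 randomised patients (15, 33 and 50 per arm), complete outcomes for everyone at each look, and a flag if one-sided Fisher exact p < 0.05 for more deaths in the intervention arm. Single-look figures sum exact binomial probabilities. The three-look figures are by simulation on accumulating data.

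| Mortality, intervention vs control (assumed) | 15 per arm | 33 per arm | 50 per arm | Any of three looks |
|---|---|---|---|---|
| 60% vs 30% | 36% | 74% | 88% | about 90% |
| 50% vs 30% | 18% | 41% | 57% | about 63% |
| 45% vs 30% | 11% | 26% | 38% | about 44% |
| 35% vs 35% (false alarm) | 2.0% | 2.7% | 3.3% | about 6% |

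If an excess in either arm raised a flag, the false-alarm rates would be 4.0%, 5.5% and 6.6% per look and about 12% over three looks.

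A wider look at 30 patients alone would detect little. The gain comes from repeating it.

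**The case against.** **Silence of a condensed article.** A reader might infer that this is the trial's only safety review and that an excess of deaths would stay unseen until the end. The article does not say so. It condenses a full protocol that is not shown, and later committee meetings, SAE reporting or a charter are commonly left to that document. This stands: the point is confined to the rule that the article states.

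**Scope of the restriction.** The limit on unblinding opens with words that tie it to that one assessment. It does not bar the committee from other data at other times. Restricting interim unblinding also has a legitimate purpose when mortality leads the primary endpoint of an open-label trial. Both observations stand, but neither makes the criterion at that assessment sensitive to unattributed deaths.

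**Breadth of attribution.** Any fatal event is an SAE, and the threshold is low: the physician need only believe that it might be related. There is also a second, procedure-based criterion. So it would be wrong to say that a mortality excess triggers nothing; it need trigger nothing. How often physicians would attribute such deaths cannot be known from the documents. On the other side, a single attributed event means that safety is not established, which may discourage attribution.

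**Size of the gain.** A doubling of mortality from 30% to 60% is an extreme case. For 45% against 30%, three looks still miss more than half. Outcomes also lag randomisation, so real sensitivity would be lower than tabulated. This stands and is carried into the verdict.

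**Direction of the flag.** Flagging excess control deaths would amount to a look for benefit and would double the false alarms. The proposal is therefore confined to one direction.

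**Conclusion.** The concern holds as a criticism of a stated rule, not of missing detail. Followed as written, the continuation criterion makes no comparison between arms and registers deaths or organ failure only if they occur in the intervention arm, during allocated treatment, and are attributed by an unblinded physician. The article describes no later safety review for 102 of 132 patients (77%), though one may exist elsewhere.

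The size of the gain from by-arm review depends on assumed mortality, because the article gives no rates. Three looks would flag large harm in about 90% of trials and moderate harm in about 44% to 63%, against about 6% false alarms at equal 35% mortality. These figures assume complete outcomes at each look. The change is worth making because it uses a committee and data that already exist. It does not guarantee that moderate harm would be found.

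**What to change.** - Let the existing committee see all-cause deaths, all SAEs and organ failure by arm, regardless of attribution, at the 30-patient review and at about two later reviews, for example at 66 and 99 randomised patients.
- Prestate a one-directional flag for excess deaths in the intervention arm, for example one-sided Fisher p < 0.05, that leads to committee deliberation and not to automatic stopping.
- State openly that this shows the mortality component of the primary endpoint to the committee and to nobody else, and that stopping for benefit is not allowed.
- Reconcile the two wordings of relatedness.
- If the full protocol or a charter already provides later by-arm reviews, say so in this section.

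**Cost.** The mortality and organ-failure data are already collected as endpoints, so the work is a wider table at the first review and two further reviews. The downside is a false-alarm chance of 2–3% per look and about 6% over three looks at equal 35% mortality, with limited sensitivity to moderate harm. Because the flag acts only in the harm direction, it does not raise the false-positive rate for benefit.
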